## Abstract

**Background:**

Gestational diabetes mellitus (GDM) is a common perinatal condition. Convincing evidence has shown that hyperglycemia and other chronic comorbidities of diabetes during the prenatal period increase maternal and fetal risk. Several guidelines have identified lifestyle management as the first-line therapy in GDM patients. To improve the efficacy of lifestyle intervention, cognitive behavior therapy (CBT) is proposed as a solution to improve clinical outcomes. The objective of this trial is to determine the efficacy in treating hyperglycemia of mobile-based CBT interventions in GDM patients, compared with conventional face-to-face interventions.

**Methods:**

This trial is designed as a prospective randomized controlled trial, which enrolled the patients diagnosed with GDM in First People’s Hospital of Kunshan affiliated with Jiangsu University from September 2021 to March 2023 with a 3-month follow-up. The specific randomization method was established and implemented through the central randomization system of EDC clinical trials. The percentage of all blood glucose levels collected within the normal range between the two groups at baseline, during the intervention period, and postpartum infant and maternal outcomes will be measured. Summary statistics for continuous variables will include the number of subjects, mean, median, SD, or the standard error, minimum, and maximum. The chi-square test, *t* test, and paired-sample *t* test were used for statistical analysis of differences between groups.

**Discussion:**

This trial investigates the effects of mobile-based CBT intervention on blood glucose levels in GDM patients.

**Trial registration:**

Chinese Clinical Trial Registry (ChiCTR2100048527) [registered: 2021/07/09].

## Strengths

We propose an approach in which researchers and participants are involved throughout the entire process, from data collection to the action plan. The algorithms of the system are developed by collecting real patient data, establishing disease databases and disease models. Accordingly, this system will accommodate the Chinese population more appropriately.Traditional CBT intervention is delivered face-to-face, which has the limitation of time-consuming and location-specific. Our mobile-based intervention system is developed independently by a professional team based on the theories of computerized CBT. It is characterized by a self-service intervention method. This allows our CBT intervention to overcome these limitations and makes it more accessible to the patients.It is expected to benefit the patients when considering the cycle of disease in disease management. From the perspective of a patient’s journey, this intervention realizes systemic management of disease with a seamless connection between in-hospital care and home-based care. As a result, this can bring more value to the patients.

## Limitations

This study excludes pregnant women whose past medical history include diabetes and only investigates women developing diabetes after pregnancy. Future studies could involve a larger patient group.Due to the nature of the research, it is impossible to blind participants and staff (excluding statisticians) in psychotherapy studies. Consequently, therapy expectancy effects may be a source of bias.

## Introduction

Gestational diabetes mellitus (GDM) is a common perinatal condition accompanied by glucose intolerance throughout pregnancy. Convincing evidence has shown that hyperglycemia and other chronic comorbidities of diabetes during the prenatal period increase maternal and fetal risk, including spontaneous abortion, fetal abnormalities, and pre-eclampsia [1, 2] Several guidelines have identified lifestyle management as the first-line therapy in GDM patients [3–5]. Due to the fact that most oral anti-diabetic medications cross the placenta or lack safety data in treating GDM, there is a considerable demand for a non-pharmacological treatment of GDM patients. For most patients, lifestyle management is sufficient to treat GDM [4, 5]. Insulin should be considered to achieve glycemic goals if necessary [3, 6]. Currently, nutrition and physical activity counseling are primary tools for lifestyle intervention. However, the gap between hospital and home has restricted continuous and thorough treatment and follow-up. Considering how to provide lifestyle interventions to promote better clinical outcomes, we sought to determine an effective method to provide GDM patients with efficient and structured lifestyle interventions [5].

Cognitive behavior therapy (CBT) is a goal-directed and systematic psychological therapy created by A.T. Beck in the 1960s to manage out-of-control emotions, behavior, and cognition [7]. CBT focuses on increasing self-efficacy through cognitive and behavioral changes, which benefits patients in terms of clinical results [8]. In GDM patients, glucose management involves everyday decision-making, including food choices, appropriate physical activities, monitoring blood sugar, and stress management [9]. Previous study has suggested that participants who become aware of their unhealthy behavior will intrinsically be driven to change. In these patients, clinical outcomes are improved with practical tools for long-term proactive behavioral change [10]. With regard to what we utilize as our tools, we suppose lifestyle management delivered with CBT will benefit GDM patients from the positive impact on compliance and long-term performance, and we consider that mobile-based CBT can potentially improve clinical outcomes in GDM patients.

Major components of lifestyle modification in GDM patients include nutrition therapy and weight management [3, 11]. These factors depend on patients’ self-efficacy, which theoretically can be improved by computerized CBT. In consequence, we suppose that CBT-based lifestyle intervention is effective in reducing glucose levels in GDM patients.

### Evidence before this study

Improved self-efficacy is a key component of lifestyle adjustment, which has been correlated with improved clinical results in GDM patients. Traditionally, patients are seen in an outpatient setting where healthcare experts can deliver lifestyle interventions to them face to face. However, the limitation of time-consuming and location-specific has been an obstacle for GDM patients to receive a consistent intervention. To encourage healthy lifestyles, novel intervention methods have been developed, including mobile-based interventions. We searched PubMed for researches that had investigated the use of CBT in diabetic patients from November 2016 to November 2021. Search terms included diabetes, gestational, pregnancy, mobile-based, and cognitive behavioral therapy. MeSH (Medical Subject Headings) was used to include synonyms. Based on our review, several studies have shown that CBT is effective in improving subjective data such as depression and social and occupational functioning in diabetic patients, but none was found to investigate objective findings in GDM populations. We identified two randomized controlled studies that have investigated the efficacy of CBT in T2DM patients. The results prove that CBT interventions significantly reduce diabetes-related distress (DRD) and hemoglobin A1c (HbA1c) compared with the control group (*n* = 56, *n* = 222) [12, 13]. Another randomized controlled trial has investigated the efficacy of lifestyle interventions in reducing the risk of developing diabetes and cardiovascular disease. Evidence has shown that compared with health brochures, lifestyle intervention such as motivational interview was not more effective in reducing the risk in an at-risk population (*n* = 622) [14].

### Added-value of this study

Most of the previous studies target T2DM patients, but there is limited information on CBT’s effect on GDM populations, who are recommended to be treated with lifestyle intervention as first-line therapy [3–5]. In addition, our study is designed to evaluate CBT’s efficacy in infant and maternal outcomes. Researchers have attributed GDM to an increased risk of fetal adverse events, including neonatal infection [15]. This study will further evaluate the efficacy in parameters measuring these outcomes, such as the case number of low-birth-weight neonates and comorbidity of GDM in participants.

### Objectives

Aim 1: To determine the efficacy in treating hyperglycemia of mobile-based CBT interventions in GDM patients, compared with conventional face-to-face interventions.Hypothesis 1a (primary study hypothesis): a significant difference in the percentage of blood glucose levels within a normal range is expected between the two groups. The normal range is defined as fasting blood glucose.

Aim 2: To determine the efficacy of mobile-based CBT interventions in infants and maternal outcomes, compared with conventional face-to-face interventions.Hypothesis 2a: a significant difference in the variables evaluating infants and participants outcomes, including low-birth-weight neonates, neonatal macrosomia, events of hypoglycemic events in infants, and cesarean delivery, is expected between two groups.

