#### Secondary outcome measures

1) The percentage of blood glucose levels collected within the normal range on each selected examination day.2) Loss of self-monitoring rate.3) HbA1c.4) Mean score of Diagnostic and Statistical Manual of Mental Disorders (DSM-5) assessment. DSM–5 is developed as a standard classification system for mental disorders. It provides a guideline of structured clinical interviews utilized to diagnose depression [18]5) Mean score of General Self-Efficacy Scale (GSE). The GSE is a psychometric scale that measures the confidence in one’s capacity to deal with a wide range of life’s issues. The test consists of ten items that describe attitudes toward barriers and are assessed on a scale of 0 (least optimal) to 4 (very optimal). A version in Chinese translation has been approved [19]6) Any insulin dose prescribed.7) Case number of low-birth-weight neonates. Low birth weight is defined as the first weight recorded after the birth of less than 2500 g (up to and including 2499 g) [20]8) Case number of neonatal macrosomia. Neonatal macrosomia is defined as the first weight recorded after the birth of more than 4000 g (more than and including 4000 g) [21].9) Hypoglycemic events in neonates (blood glucose < 2.2 µmol/L).10) Other fetal adverse events.11) Case number of GDM comorbidity developed during the intervention period.12) Case number of cesarean delivery.13) Total expenditures for delivery.

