### Statistical methods

#### Statistical methods for primary and secondary outcomes

Categorical variables will be expressed in numerical values with their respective percentages and compared using the chi-squared test at baseline. Continuous variables will be expressed as mean ± SD and compared using the *t*-test. The significance of primary and secondary endpoints will be evaluated with the paired-samples *t*-test. A *p*-value < 0.05 indicates statistical significance. All data will be analyzed with the SPSS.

All patients who have received CBT for at least 4 weeks will be included in the full analysis set (FAS). Depending on the time investigated, the per-protocol (PP) analysis set will be made up of patients who complete the 6-month follow-up examinations. The FAS will be used as the basis for the primary analysis. If there is a discrepancy of greater than 10% between the FAS and PP samples, the analysis will be repeated for the PP analysis set. The safety population will include patients in the FAS. Unless otherwise noted, all analysis will be done in both the FAS and PP analysis sets. No additional analysis will be conducted.

There will be no replacement or imputation of missing values. All analysis will be based solely on observed cases. Patients who loss to follow-up will be considered to have dropped out of therapy. Only the PP patients will be used in a sensitivity analysis to test the impact of this assumption.

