## Discussion

This article presents a detailed description of a parallel, randomized control trial, designed to evaluate the effectiveness of CBT to reduce hyperglycemia in GDM patients. Lifestyle intervention is recommended as the first-line treatment for GDM per guidelines. To accomplish the primary goal of controlling blood glucose, we consider the mobile-based CBT intervention as an available and accessible method with regard to how to promote healthy habits, and as a result, this will potentially lower blood glucose in ASCVD patients. We believe that mobile-based CBT lifestyle intervention will be potentially effective in lowering blood glucose levels in ASCVD patients.

This study has some critical implications. The novel mobile-based lifestyle intervention is expected to reduce glucose level at a population level due to the high accessibility and availability of technologies. Moreover, this study can potentially demonstrate CBT-based lifestyle intervention’s efficacy in infant outcomes and be utilized as a future guidance for lifestyle intervention in GDM patients.

There are some limitations of this study. First, this study excludes pregnant women whose past medical history include diabetes and only investigates women developing diabetes after diabetes. Future studies could involve a larger patient group. Second, it is impossible to blind participants and staff (excluding statistician) in psychotherapy studies due to the nature of the research. As a result, therapy expectancy effects may be a source of bias.

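### Aim 2 is an efficacy hypothesis on at least four secondary outcomes at unadjusted p < 0.05, with no order, no gate from Aim 1 and no success rule

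*Protocol article*

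**What the plan says.** The Objectives section sets two aims in parallel form. Aim 1 concerns hyperglycemia, and its hypothesis alone is ranked: "Hypothesis 1a (primary study hypothesis". Aim 2 is "To determine the efficacy of mobile-based CBT interventions in infants and maternal outcomes, compared with conventional face-to-face interventions". Hypothesis 2a then expects "a significant difference in the variables evaluating infants and participants outcomes, including low-birth-weight neonates, neonatal macrosomia". The list is left open and runs in full: "including low-birth-weight neonates, neonatal macrosomia, events of hypoglycemic events in infants, and cesarean delivery, is expected between two groups". Hypothesis 2a gives no direction and carries no label of its own.

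All four named outcomes appear under Secondary outcome measures, as items 7, 8, 9 and 12 of 13.

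The section on statistical methods for primary and secondary outcomes evaluates the significance of both kinds of endpoint by the same rule, "A *p*-value < 0.05 indicates statistical significance", and adds that no further analysis is planned. It mentions no adjustment, no testing order and no exploratory status.

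The Discussion states the intended use of the results: "this study can potentially demonstrate CBT-based lifestyle intervention’s efficacy in infant outcomes and be utilized as a future guidance for lifestyle intervention in GDM patients".

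**The concern.** A secondary label normally tells the reader that an outcome is supportive. Here the protocol attaches to these secondaries an aim of their own, a hypothesis worded in terms of significance, and a prospective efficacy claim in the Discussion. It then fixes the threshold for each test but not how the tests combine into a conclusion on Aim 2.

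Nothing would stop a report from taking one birth outcome at p < 0.05 as support for Hypothesis 2a, even after a null glucose result and whichever group it favored. The trial is sized on the glucose percentage alone, so a lone significant result on an uncommon neonatal event would be weak evidence. The protocol nevertheless foresees such results guiding later care.

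**Working it through.** **Inputs from the protocol article**
- Outcomes named in Hypothesis 2a: k = 4 (Objectives). The list is open, so four is a minimum.
- Per-test threshold: 0.05 (Statistical methods). No family-wise rate is stated, so there is no plan figure of that kind to reproduce.
- Sample size: 80 per group, raised for 20% attrition to 80 / (1 − 0.20) = 100. That step reproduces, but the calculation concerns the glucose percentage only and gives no assurance for the Aim 2 outcomes.

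**Assumptions, not in the protocol**
- One significant outcome is enough to support Aim 2.
- No true difference exists in any of the four (complete null).
- Each test has size exactly 0.05, and is two-sided where correlation enters. The correlation values are assumed.

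**Step 1: independent tests**

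P(at least one false positive) = 1 − (1 − 0.05)^4 = 1 − 0.8145 = 0.1855, or 0.1855 / 0.05 = 3.7 times the per-test level. This result depends only on the test size, so it is the same for one-sided and two-sided tests.

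**Step 2: equally correlated two-sided tests**

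With c = 1.96 and X standard normal, P = 1 − E[{Φ((c − √ρ·X)/√(1−ρ)) − Φ((−c − √ρ·X)/√(1−ρ))}^4], evaluated numerically:

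| Assumed ρ | P(at least one) | Multiple of 0.05 |
|---|---|---|
| 0 | 18.5% | 3.7 |
| 0.3 | 17.4% | 3.5 |
| 0.5 | 15.6% | 3.1 |
| 0.8 | 11.4% | 2.3 |

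A common correlation as high as 0.8 is unlikely. By the protocol's definitions (under 2500 g; 4000 g or more) one neonate cannot have both low birth weight and macrosomia. At assumed rates of 5% and 8%, the correlation between those two events is −√[(0.05 × 0.08) / (0.95 × 0.92)] = −0.07, close to independence.

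**Step 3: uncommon binary events**

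Tests on sparse counts may not reach their nominal size. At 80 per arm and assumed event rates of 5%, 8%, 3% and 40%, the uncorrected chi-squared test has exact sizes 0.0417, 0.0459, 0.0432 and 0.0472. If independent, P = 1 − (0.9583 × 0.9541 × 0.9568 × 0.9528) = 0.167. This is illustrative only. The Statistical methods section mentions chi-squared for baseline comparisons and names a paired-samples *t*-test for the endpoints.

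**Step 4: the other success rule**

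If all four outcomes had to be significant, the false-positive chance could not exceed the smallest single-test size, 5%, and there would be no inflation. The size of the problem therefore depends on a rule that the protocol does not give.

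**The case against.** The strongest reply is that this is an ordinary design: one primary hypothesis, one endpoint used for sizing, and secondaries reported at nominal 0.05. Much of that stands. A primary/secondary ranking exists, so it would be wrong to say that the protocol has no hierarchy. What is missing is narrower: an order among the Aim 2 outcomes and a gate from Aim 1. The error rate of Hypothesis 1a is not inflated.

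It is also fair that the protocol never calls Aim 2 confirmatory. That is an inference from its wording, and the Discussion says only that the study can potentially demonstrate efficacy. The rule that any one outcome suffices is likewise a reading. Hypothesis 2a joins its outcomes with a conjunction, and a sponsor could say that all were meant.

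An unseen analysis plan might add an adjustment. But the protocol is not silent: it sets the threshold for secondaries and writes a significance hypothesis on them. A later plan would be changing that rule, and the objective and the Discussion would still need rewording.

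A reader might go further and count all 13 secondaries, down to "Total expenditures for delivery", or a separate test for every examination day under item 1, "The percentage of blood glucose levels collected within the normal range on each selected examination day". Neither count measures the Aim 2 claim. The 13 include items such as HbA1c, self-efficacy and cost that Hypothesis 2a does not name. Item 1 defines a measure, and no test for each day is specified.

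**Conclusion.** The point holds in limited form. Aim 2 is worded as an efficacy hypothesis on at least four secondary outcomes, each judged at unadjusted 0.05, without an order, a gate from the primary or a success rule. If one significant result is taken as enough, the chance of at least one false positive among the four is about 18.5% under independence, 15.6% at an assumed correlation of 0.5 and 11.4% at 0.8.

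Those figures rest on the any-one reading and the complete null. With only three or two of the four truly null, the independent figures are 1 − 0.95^3 = 14.3% and 1 − 0.95^2 = 9.8%.

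A reader might conclude that the trial's stated error rate is wrong by a factor of about three. The document does not support that. It states a per-test level and no family-wise rate, and a factor near three needs a correlation of about 0.5 to 0.6 or conservative tests of rare events. The primary analysis is not compromised on this ground. The point bears on what may be claimed for birth outcomes, and the text should be changed before results are known.

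**What to change.** **Preferred.** In the Statistical methods section, state that p < 0.05 is confirmatory for Hypothesis 1a only. Report the Hypothesis 2a outcomes and the other secondaries as effect estimates with 95% confidence intervals, labelled exploratory. Reword Hypothesis 2a as estimating the effect on infant and maternal outcomes, and bring the Discussion sentence on infant outcomes into line.

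**If a formal Aim 2 claim is to be kept.** Close the list at the four named outcomes. Test them by Holm's procedure at 0.05, only if the primary is significant, and label the remaining secondaries exploratory. The ordered p-values are then compared with 0.05/4 = 0.0125, 0.05/3 = 0.0167, 0.05/2 = 0.025 and 0.05. State that the tests are two-sided, since Hypothesis 2a gives no direction.

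**Cost.** A few sentences in the objectives, methods and Discussion, with no new patients or data. Under either option, an isolated p < 0.05 on a birth outcome could no longer be presented as demonstrated efficacy. The Holm option also sets a stricter first threshold for outcomes on which the trial was not sized.

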### Trial design

This study is a single-center, randomized, controlled, open-label parallel-group superiority trial. Patients will be randomly allocated at a 1:1 ratio to evaluate the efficacy of CBT to lower blood glucose in GDM patients. The study protocol follows the Standard Protocol Items: Recommendations for Interventional Trials (SPIRIT) [16].

## Methods: participants, interventions, and outcomes

### Study setting

The study will be performed at the First People’s Hospital of Kunshan affiliated with Jiangsu University, Kunshan, Jiangsu Province, China, from September 2021 to March 2023.

### Eligibility criteria

#### Inclusion criteria

Patients’ inclusion criteria will be as follows: (1) age from 18 to 45 years old; (2) pregnant women who completed oral glucose tolerance tests (OGTT) at 24–28 gestational weeks; (3) meet diagnostic criteria of GDM and has not received pharmacological therapy; (4) no difficulty in using smartphones, basic Chinese reading and writing skills, basic calculation skills; (5) agree to sign the informed consent form.

#### Exclusion criteria

Patients’ exclusion criteria will be as follows: (1) prior diagnosis of diabetes before pregnancy; (2) prior diagnosis of GDM in previous pregnancy; (3) diagnosed with severe mental disorders or has difficulty understanding; (4) other conditions that could prevent the patients from participating in the research. This trial does not exclude any other concurrent therapies or interventions. The number and doses of insulin prescriptions will be recorded.

Researchers will perform an initial eligibility screening and collect written informed consent from enrolled participants. Written informed consent will be collected prior to the baseline assessment. If the data collection is not included in the initial informed consent process for the main clinical trial, each participant in the ancillary study must sign a consent form.

